## Abstract

**Background:**

To date, the establishment and development of palliative day-care clinics and day hospices in Germany have been completely unsystematic. Research is needed to gain insight into these services and to ensure their accessibility and quality. Accordingly, the ABPATITE research project aims at: (1) identifying the characteristics of palliative day-care clinics and day hospices in Germany, (2) determining demand and preferences for these services, and (3) proposing recommendations (with expert agreement) for the needs-based establishment and development of these services.

**Methods:**

The research is a multi-perspective, prospective, observational study following a mixed-methods approach across three study phases. In phase 1a, qualitative expert interviews will be conducted to capture the facility-related characteristics of palliative day-care clinics and day hospices in Germany; the results will feed into a questionnaire sent to all such institutions identified nationwide. In phase 1b, a questionnaire will be sent to local statutory health insurance providers, to gain insight into their contracts and accounting and remuneration models. In phase 2a, a service preference survey will be conducted with patients and family caregivers. In phase 2b, semi-structured interviews with management staff will explore the factors that promote and hinder the provision of service. In phase 2c, the external perspective will be surveyed via focus groups with local actors involved in hospice and palliative care. In phase 3a, focus groups with representatives from relevant areas will be conducted to develop recommendations. Finally, in phase 3b, recommendations will be agreed upon through a Delphi survey.

**Discussion:**

The empirically developed recommendations should enable the establishment and development of day hospices and palliative day-care clinics in Germany to be better managed, more oriented to actual demand, and more effectively integrated into wider health care services. Importantly, the findings are expected to optimize the overall development of hospice and palliative care services.

**Trial registration::**

The study was prospectively registered in the German Clinical Trials Register (Deutsches Register Klinischer Studien) (Registration N° DRKS00021446; date of registration: April 20, 2020). The study is searchable under the International Clinical Trials Registry Platform Search Portal of the World Health Organization, under the German Clinical Trials Register number.

## Background

In Germany, trans-sectoral inpatient and ambulatory hospice and palliative care services for people with incurable, progressive illnesses and limited lifespans have significantly advanced in recent years, in both specialized and general sectors. More than likely, this is due to the socio-political relevance of and support for end of life care in Germany, where inpatient hospices, palliative care units, ambulatory hospice services, and specialized palliative home care services are widely established.

The Hospice and Palliative Care Act 2015 has placed a greater focus on strengthening and expanding general palliative care in Germany [1]. Specifically, this dynamic law aims at establishing needs-oriented, comprehensive care services in both urban centers and economically weak and rural regions, as well as improving access to all hospice and palliative care services, particularly for immigrants and members of socially disadvantaged groups (e.g. prisoners). This promotion of a needs-based, patient-oriented approach to hospice and palliative care also applies to palliative day-care clinics and day hospices [2]. While these services are not necessarily defined by social law in Germany, they must still adhere to regulations in order to successfully claim costs back from statutory health insurance providers. Day-care services are often linked to institutions such as inpatient hospices and palliative care units or hospitals; however, they may also operate independently. The primary aims of these day-care institutions, in which patients spend up to five days per week, are maintaining patients’ autonomy, improving patients’ quality of life, and supporting family caregivers by granting them “respite care” [3].

To date, the establishment and development of palliative day-care clinics and day hospices in Germany have been completely unsystematic. Thus, existing institutions may have implemented—and may continue to implement—insular solutions that are not coordinated with other institutions or with regional health care services, or indeed with the general health care services covered by statutory health insurance providers. For this reason, patients at their end of life may find that these institutions are not sufficiently integrated into the German health care system. In Germany, structural standards and quality indices for palliative day-care do not exist, and the label of “day hospice” is applied to practices that are very heterogeneous, in terms of services offered. This can generate confusion among patients and family caregivers, making it difficult for them to choose an adequate and needs-oriented form of care. However, standards do exist for services financed by statutory health insurance providers, and these standards ensure a high quality of care [4].

### Investigating the status of and demand for palliative day-care clinics and day hospices

In 2010, the European Association for Palliative Care estimated that one palliative day-care clinic or day hospice was needed for a catchment area of 150,000 residents [5]. More recent surveys of demand in Germany have investigated palliative day-care clinics and day hospices only marginally, or not at all [6–8]. Internationally, mostly qualitative interview studies and quantitative surveys and analyses of patient records show a high level of patient satisfaction with the quality of care received at palliative day-care clinics and day hospices, relating to the opportunities for social participation offered by these institutions and their maintenance of quality of life [9, 10]. However, systematic findings from controlled studies of high methodological quality are lacking, particularly in relation to the effectiveness of these end of life institutions in: improving symptoms, providing inter-sectoral continuity of care, preventing inpatient hospital admissions and nursing home or hospice admissions, and delivering cost savings across the course of a disease [11, 12]. Notwithstanding the scientific evidence for the need and effectiveness of day-care services in Germany, initiatives to establish palliative day-care clinics and day hospices are evolving [13–22].

### Study aims

Scientific research is needed to provide an overview of current hospice and palliative day-care services in Germany; to increase the transparency of these services over the long term; and to ensure the accessibility and quality of these services. In response to this need, the ABPATITE consortium study aims at answering the following questions, across three phases:

Phase 1: What palliative day-care clinics and day hospices are operating or in development in Germany, and what are the characteristics of these facilities?

Phase 2: What is the demand for palliative day-care clinics and day hospices in Germany, as assessed by health care professionals, stakeholders, and representatives, and what are the service preferences of patients and family caregivers?

Phase 3: What recommendations can be determined and agreed upon for the needs-based establishment and development of day hospices and palliative day-care clinics in Germany?

### Aims of the study protocol

The present research is a mixed-methods study involving qualitative and quantitative methods and participatory aspects. The project aims at making an original contribution to the palliative care literature by increasing the transparency of palliative day-care clinics and day hospices in Germany. Publication of the study protocol represents the first step in this process. In their previous Dy@EoL project [23], the authors experienced that recruitment partners and scientists studying similar topics were interested in consulting the study protocol to obtain an overview of the project. Furthermore, the processes of establishing and developing institutions and measuring status and demand in palliative day-care clinics and day hospices are not necessarily straightforward. The present study protocol is designed to shed light on these processes. In addition, the study protocol addresses ethical considerations, data security, and the dissemination and implementation of the study results. Finally, the study design for systematic research on palliative day-care clinics and day hospices is of relevance to the scientific community.

## Methods and design

The present multi-perspective, prospective, observational study follows a mixed-methods approach, spread across three research phases. The study protocol adheres to STROBE guidelines [24].

In phase 1a, palliative day-care clinics and day hospices in Germany are being identified through national online databases of hospices and palliative care providers [25, 26] and general Internet searches. Exploratory, qualitative expert interviews are being conducted (currently underway) with facility managers to capture relevant facility-related characteristics. These results will be used to develop a standardized quantitative questionnaire that will be sent to all palliative day-care clinics and day-hospices identified nationwide.

In phase 1b, a quantitative, standardized instrument will be developed in cooperation with a local statutory health insurance provider (AOK Lower Saxony) to identify and record all day hospices and palliative day-care clinics that are contracts with the statutory health insurance funds. The instrument will not only record the contractual partners, but it will also capture contractual terms relating to remuneration and services provided, as well as the number of patients treated in these facilities. Further, the number of claims and approvals filed by the day hospices and palliative day-care clinics will be collected.

In phase 2a, a preference survey about hospice and palliative care will be administered to patients with a potentially palliative course of illness and their family caregivers. The aim of this quantitative step will be to determine the preferences of patients and their family caregivers regarding palliative care services they may draw on in the future. The questionnaire will contain a case description of a patient in palliative care, as well as a discrete choice experiment (DCE) [27, 28]. In the DCE, participants will be asked to choose between two alternative palliative care situations. From the DCE data, conclusions will be drawn about the perceived importance of individual care characteristics. The questionnaire will also capture patients’ socio-demographic and medical data (related specifically to their disease), as well as data on family caregivers’ willingness or capacity to provide care. A literature search and expert discussion with representatives of the German Association for Palliative Medicine and the German Hospice and Palliative Care Association will inform the design of the questionnaire and DCE. The validity, comprehensibility, and feasibility of the questionnaire will be tested in a pre-test with patients and family caregivers, using the verbal probing technique [29]. To minimize the risk of response bias, the questionnaire will be formulated in a way that is generally understandable and can be completed independently by patients and relatives.

In phase 2b, semi-structured (telephone) interviews with managers from three to five selected day hospices and palliative day-care clinics in Germany will be conducted as case studies (*N* = 6–10 persons; two persons in different functions per facility). The interview guide will comprise open, stimulating questions with the aim of highlighting thematic complexes such as local networking with hospice and palliative care providers. After each interview, the guide will be reviewed and adapted. The objective of this phase will be to explore the conditions under which the respective facilities have evolved, identify the factors that promote and hinder their service provision, and elicit information on their integration into regional hospice and palliative care networks from an internal perspective. The external perspective on day hospices and palliative day-care clinics in Germany will be surveyed in phase 2c by way of focus groups [30, 31] with local actors involved in hospice work and palliative care (e.g. actors affiliated with ambulatory palliative home care, specialized palliative home care, in-patient hospices, palliative care wards, long-term care support centers, and municipalities). The results of phase 2b will be used to identify potential participants.

Using a participatory action research methodology [32], in phase 3a, 2-hour focus groups with representatives from relevant areas (e.g. the German Association for Palliative Medicine, the German Hospice and Palliative Care Association, the German College of General Practitioners and Family Physicians, the German Home Care and Nursing Society, the German Association of Towns and Municipalities, the National Association of Statutory Health Insurance Physicians, regional Associations of Statutory Health Insurance Physicians, the German Medical Association, the Association of German Cities, the National Association of Statutory Health Insurance Funds, the Association of Private Health Insurance Companies, and social and health policy) will be conducted to develop recommendations for the needs-oriented establishment and development of day hospices and palliative day-care clinics in Germany.

Finally, in phase 3b, the empirically derived recommendations from phase 3a will be agreed upon via a Delphi survey [33] with experts, including participants from phase 3a.

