### Study population and data collection

Following a descriptive analysis of the initial search data from phase 1a, a heterogeneous group of palliative day-care clinic and day hospice managers (approx. *n* = 6) (from facilities of varying sizes, years of operation, urban vs. rural areas) will be recruited to participate in a qualitative telephone interview. The exact number of interviews will be determined during the course of study, on the basis of the minimum number needed to represent relevant institution-related criteria. Similarly, the final number of palliative day-care clinics and day hospices to be surveyed will be determined during this study phase. In phase 1b, the standardized written survey will be distributed to all 11 local statutory health insurance providers (AOK).

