### Data analysis

The data analysis will aim at describing the current situation and demand for palliative day-care clinics and day hospices in Germany, and determining agreed recommendations for the establishment and development of these services.

In phase 1a, quantitative data from the online searches (i.e. a national database and general Internet search) and the palliative day-care clinic and day hospice survey will be transferred to an electronic database using IBM SPSS Statistics 26 (SPSS Inc., Chicago, IL, USA) for Windows. The data will then be analyzed using descriptive and frequency statistics. Interviews will be recorded on tape, transcribed verbatim by an external party, and analyzed qualitatively in MaxQDA (VERBI Software Consult Sozialforschung GmbH, 1989–2020), using the methodological principles of qualitative content analysis [34, 35]. Characteristics that have already been determined for the institutions will comprise an a priori category system, which will be successively expanded with the interview data. The results will provide an extended overview of the defining characteristics of these institutions, based on primary information from facility managers.

In phase 1b, the collected data on insurance providers and their contractual partners will be integrated to produce an overview of day hospices and palliative day-care clinics. Quantitative data will be evaluated using descriptive and frequency statistics.

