## Conclusions

The present study protocol explains the purpose, significance, and scope of the mixed-methods ABPATITE study, as well as the study design. The empirically developed recommendations generated by this study are expected to optimize the establishment and development of day hospices and palliative day-care clinics in Germany, by ensuring they are better managed, more oriented to actual demand, and more effectively integrated into wider health care services. The results may also inform structural changes to the legal framework (e.g. to promote a framework agreement between the statutory health insurance umbrella association and health service providers). Finally, the empirically developed recommendations may be recast as a practice guide for the establishment and development of palliative day-care clinics and day hospices in Germany.

The authors’ goal of publishing the present study protocol is to promote transparency by facilitating open access to comprehensive study details that extend beyond the summary publicized in the German Clinical Trials Register. Moreover, the study protocol may act as a point of reference for the scientific community and other parties interested in the scientific and ethical aspects of the study, and prevent unnecessary duplication.

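### Phase 1b is worded as a record of all facilities contracted with the statutory health insurers, but it surveys only the 11 AOK funds, so it supports statements only about AOK contracts and AOK-reported counts

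*Protocol article*

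**What the plan says.** Under *Methods and design*, the protocol article gives the purpose of the phase 1b instrument as "to identify and record all day hospices and palliative day-care clinics that are contracts with the statutory health insurance funds". It is also to capture contractual terms on remuneration and services, "as well as the number of patients treated in these facilities", and further, "the number of claims and approvals filed by the day hospices and palliative day-care clinics will be collected". None of these quantities is limited to one type of fund.

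The recipients are fixed under *Study population and data collection*: "the standardized written survey will be distributed to all 11 local statutory health insurance providers (AOK"). The abstract is closer to this narrower frame: "a questionnaire will be sent to local statutory health insurance providers, to gain insight into their contracts and accounting and remuneration models".

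Under *Data analysis*, "the collected data on insurance providers and their contractual partners will be integrated to produce an overview of day hospices and palliative day-care clinics", using descriptive and frequency statistics. The overview is not confined to AOK contracts or AOK-insured patients.

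**The concern.** The stated target is every facility contracted with the statutory funds as a group. The survey frame is one family of funds within that group. Both statements are in the current text, so this is not a matter of detail that a condensed article leaves to a fuller document.

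A facility whose contracts are only with other funds cannot enter the phase 1b list. Even where an AOK contract exists, an AOK fund would be expected to know the attendances, claims and approvals of its own insured persons, not those of other funds' members. The article nevertheless words these counts as belonging to the facilities.

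What is at stake is how the descriptive figures are read. Patient and approval numbers reported without a label could be taken as facility totals when they are one payer's part of them. They would also be hard to compare between facilities if the AOK share differs from one to another. Phase 1b is the only phase described as surveying insurers on contracts and remuneration, so no other insurer survey would reveal or correct the gap.

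**Working it through.** The article's own figure here is 11. It is a full count of the AOK funds, not a calculated sample size, so there is nothing to reproduce. The check sets target, frame and analysis side by side.

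| Element | Where | Scope as written |
|---|---|---|
| Facilities to be recorded | *Methods and design* | all those contracted with the statutory funds |
| Patients, claims, approvals | *Methods and design* | those of the facilities, no fund named |
| Recipients | *Study population and data collection* | 11 AOK funds |
| Recipients and content | Abstract, *Methods* | local statutory insurers and their own contracts |
| Output | *Data analysis* | overview of the facilities, no AOK limit |

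**Is the statutory sector wider than AOK?** The article treats it so. Among the bodies to be represented in phase 3a it lists "the National Association of Statutory Health Insurance Funds", and it calls the AOK funds the local providers. It nowhere equates AOK with the whole statutory sector.

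**Does anything bridge the gap?** No section sends the phase 1b survey to another fund, states what share of contracts or patients AOK covers, or says that an AOK contract also binds other funds. *Study risks* mentions selection effects for phase 2a only.

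**Patients, claims and approvals.** Let *s* be the AOK share of a facility's statutory activity and *T* its total. If each fund reports only its own insured persons, phase 1b records *s* × *T* and misses (1 − *s*) × *T*. The article gives no *s*, so the values below are assumptions:

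- *s* = 0.7: missed 1 − 0.7 = 30%
- *s* = 0.5: missed 1 − 0.5 = 50%
- *s* = 0.3: missed 1 − 0.3 = 70%

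Only *s* = 1 would give the complete count that the wording promises.

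**Comparison between facilities.** Two facilities with the same *T* but shares of 0.7 and 0.3 would appear to differ by a factor of 0.7 / 0.3 = 2.3. This shows only what unequal shares would do. The article does not say whether shares differ.

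**Facilities and contract terms.** The same formula does not apply. If contracts are concluded jointly across funds, one AOK reply reveals the facility and its terms, and coverage could approach 100%. If they are concluded fund by fund, coverage is lower by an amount that the article does not allow one to work out.

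**The study's facility list.** Phase 1a searches national databases and the internet, places calls for feedback in two association newsletters, and sends a questionnaire to every facility identified. None of this passes through an insurer.

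**The case against.** The best defence is that the AOK scope is openly disclosed. The recipients are named, and the abstract speaks of the insurers' own contracts. Read together, the broad sentence under *Methods and design* is loose phrasing. That is fair, and it means that much of the repair is a matter of wording. It does not remove the problem, because the patient, claim and approval counts and the planned overview are written without the same limit.

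Several stronger readings are tempting, and the article does not support them:

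- *That facilities without an AOK contract drop out of the study.* They drop out of the phase 1b list only. Phase 1a finds facilities independently.
- *That most activity is known to be missed.* No AOK share is given, so any percentage rests on an assumption. For facilities and contract terms there may be almost no loss.
- *That phase 1b is the intended basis for a national agreement.* Under *Conclusions*, the study's results as a whole may inform changes to the legal framework, with "to promote a framework agreement between the statutory health insurance umbrella association and health service providers" given only as an example. The recommendations themselves come from the phase 3 focus groups and Delphi survey, for which bodies representing other payers are listed.
- *That private insurers are wrongly left out.* The stated phase 1b target is statutory funds only.

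It also stands that phase 1b is descriptive, tests no hypothesis, and that *Expected results* does not list patient, claim or approval counts among the main results. Finally, the article does not list the items of the phase 1a questionnaire, so it cannot be assumed that patient numbers or funding would be absent from it.

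**Conclusion.** The mismatch is real and should be fixed, but it does not threaten the main results. As designed, phase 1b supports statements about AOK contracts and AOK-insured patients, claims and approvals, not about all statutory funds. The point is firmest for the counts, where it holds even if every contract is joint, provided that a fund knows only its own insured persons' use. Their shortfall is 1 minus the AOK share. The 30% to 70% range illustrates this for assumed shares of 0.7 to 0.3 and is not an estimate. For facilities and contract terms the size is unknown and could be close to nil.

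**What to change.** 1. Under *Methods and design*, restate the phase 1b target as facilities contracted with AOK funds, with patient, claim and approval counts as reported by those funds. Carry the same limit into the overview under *Data analysis*, and label the tables accordingly.
2. Add a few items to the phase 1a facility questionnaire: the contracting funds, total patients and, where readily available, the payer split. Facilities are the natural source of all-payer totals.
3. Cross-list the phase 1a and 1b facilities and report descriptively which appear in both and which in only one.

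Do not derive a two-source estimate of completeness from that cross-listing. Phase 1 covers facilities operating or in development, whereas phase 1b covers contracted ones, so the lists target different populations. A facility without an AOK contract also has no chance of appearing in phase 1b. Contracted facilities may in addition be easier to find in phase 1a, so independence of the two lists is doubtful.

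The alternatives are to survey the other statutory funds too, or to state and justify that AOK contracts represent all funds. The second would cover contract terms only; total patient counts would still have to come from the facilities.

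The cost is a somewhat longer facility form, some record retrieval if a payer split is requested, one matching step and a narrower stated scope. The timing is favourable: according to *Discussion* the insurer survey is still being prepared, and the facility questionnaire is to be built from the phase 1a interviews.
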